#### 2.5.9. Quality of Life (HRQoL)

The Pediatric Quality of Life Questionnaire 4.0 (PEDsQL) [67] will be used to measure the health-related quality of life in the children (HRQoL) and to assess important determinants of health such as daily activities, physical health, social interactions and emotional well-being. We will obtain the self-reported children’s HRQoL total score and the parents’ perceived children’s HRQoL total score.

#### 2.5.10. Process Evaluation of Children and Teachers

At the 6-month follow-up (T3), children and teachers will be invited to take part in focus groups meetings. These focus group sessions will allow both children and teachers to give their feedback about the active breaks intervention. Firstly, we will conduct focus groups with all the teachers of the experimental groups that performed the I-MOVE protocol. This session will be fundamental to have feedback on the efficacy, feasibility and adherence to the protocol by teachers. Secondly, we will involve teachers of the control group to be part of a focus group to understand their attitude for a future involvement in the experimental part of the project and the reason why they chose not to perform active breaks. This second focus group will be essential to outline barriers and facilitators for participation in these health promotion interventions (Appendix A). It seems very important to understand, together with the teachers, the feasibility of the project and its positive integration into daily school activities, without negative effects on children’s learning in other subjects (Math, Science, Italian and so on). In other words: the project is easily achievable and does not create problems or slowdowns in teaching other disciplines, rather it reveals positive effects on the participation and involvement of children in daily school life. This is the real wall to break down, which often prevents teachers from experimenting with new school day models.

After these two focus groups, children of the experimental classes will be involved in a discussion session. We will organize a meeting for each class that performed the I-MOVE protocol to obtain the children’s feedback about the intervention. This meeting will be managed and conducted by a researcher of our team qualified for qualitative research methods (expert in developmental psychology and education) with the supervision of class teachers (Appendix B).

Obviously, the educational network that surrounds the child also involves parents in what is called the educational triangle. Parents will also be invited to collaborate through questionnaires and discussion during the annual meetings with teachers. In all the scheduled focus groups a moderator will manage the meeting entirely, a supporter figure will help the moderator in conducting the discussion and an observer will ensure that the meeting is carried out in the best possible way.

Qualitative research together with quantitative research represents a complete strategy to measure and understand phenomena related to health [68,69].

### 2.6. Data Analysis

Data will be recorded electronically on a secure file storage system and safeguarded by a password. Data will be anonymized by assigning a unique identification number to each pupil.

#### 2.6.1. Quantitative Analysis

The statistical analysis will be performed using SPSS (Statistical Package for Social Science) (SPSS Inc. Chicago, IL, USA) The data will be reported as the mean and standard deviation for both experimental and control groups and for the T0, T1 and T2. We will use the Student’s *t*-test, (for parametric variables) the Mann–Whitney test, (for non-parametric variables) and the Chi-square test (dichotomous ones) to compare the general characteristics between the groups. Differences between the two groups from baseline to follow-up will be analyzed using a one-way ANOVA and ANCOVA adjusted for covariates. We will consider the results statistically significant only if the *p* value will be lower than 0.05. We will calculate the effect size to examine the magnitude of any mean differences.

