### 2.5. Data Collection and Outcome Measures

During the Imola Active Breaks Study the following outcomes will be evaluated: (1) PA and sedentary behaviors; (2) health related fitness; (3) motor control development during fine and gross (locomotor) tasks; (4) dietary patterns; (5) anthropometric evaluation; (6) sociodemographic and early determinants; (7) cognitive Function; (8) time-on-task behavior and (9) quality of Life.

As shown in Table 2, all the measurements will be evaluated at baseline T0 (October 2019) and will then be assessed at mid-intervention T1 (October 2020) and at the end of the intervention T2 (June 2021) to investigate group differences and changes over time. The process evaluation will performed 6 months after the end of the intervention T3 (December 2021.)

The comparisons between T0, T1 and T2 will allow the research to determine the timing of any long-term effect of ABs and whether the effects of ABs are cumulative in time or reach a ceiling after T1 (for example, if there are cumulative effects, then performance should reveal a pattern T0 < T1 < T2; by contrast, if they reach positive effects in a few months and then stabilize, then performances at T1 and T2 should not differ).

Moreover, we planned an assessment at the mid-intervention to measure an acute effect before the daily active breaks and immediately after the 10-min bout for cognitive and time on task outcomes. During this specific mid-intervention we will monitor the amount of PA performing an active break, 10 min thrice a day, during a school day for a week. This assessment will be focused on cognitive function and time-on-task behaviors, since these could be more affected after acute exercises than chronic ones, as shown for some cognitive functions in the literature [24,25,26].

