#### 2.5.3. Motor Control Development During Fine and Gross (Locomotor) Tasks

Gross- and fine-motor competences will be assessed using an instrumented approach based on wearable inertial sensors [45,46]. The selected instrumented approach allows the quantitative analysis of motor competence characteristics (e.g., automaticity, complexity and regularity) and their longitudinal monitoring as related to age and/or motor development.

For gross-motor competence 3 inertial sensors (OPAL; APDM: Portland, OR, USA) will be attached, using elastic Velcro bands, to the lower shanks (above lateral malleolus) and lower back (at L5 level) of each child over clothes, and 3D acceleration and angular velocity is acquired from each sensor during natural and tandem gait along a 15 m straight path. Each child walks 3 times back and forth normally (for a total of 45 m) and 1 time in tandem (along the straight line, positioning the heel of the front foot in contact with the toes of the back one), prior to data collection, all participants are allowed to perform a tentative trial (10 TW strides) to ensure they understand the tandem gait instructions.

For the assessment of fine-motor competence, the 3 inertial sensors (OPAL; APDM: Portland, OR, USA) will be attached to the wrists (dorsal aspect) and lower back (at L5 level), and 3D accelerations and angular velocity will be acquired during the Placing bricks test [47]. Each child, sitting at a desk, attached 18 1 × 2 Duplo bricks one at a time onto a 6 × 12 Duplo plate using one hand, then the other for the second trial; blocks will be positioned on the side of the plate corresponding to the hand to be used, while the opposite hand was kept on the table or used to stabilize the plate according to child’s preference. For all trials data are acquired at 128 Hz sampling frequency.

Temporal parameters, variability, regularity, motor complexity, stability and rhythmicity calculated from acquired motion and represented in a graphical polar plot [46] allow one to qualitatively characterize different areas of motor control performance.

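### The cumulative-versus-ceiling question across T0, T1 and T2 has no named test: section 2.6.1 compares the groups from baseline to follow-up but never T2 against T1

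*Protocol article*

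**What the plan says.** Section 2.5 (Data Collection and Outcome Measures) and Table 2 schedule most outcomes at T0 (October 2019), T1 (October 2020) and T2 (June 2021), "to investigate group differences and changes over time". The use of the three visits is explicit: "The comparisons between T0, T1 and T2 will allow the research to determine the timing of any long-term effect of ABs". Section 2.5 also gives the decision rule. On one side, "if there are cumulative effects, then performance should reveal a pattern T0 < T1 < T2". On the other, if the effect comes early and then stabilises, "then performances at T1 and T2 should not differ".

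The visits are taken on the same children. Section 2.5.3 speaks of "their longitudinal monitoring as related to age and/or motor development", and section 2.6 gives each pupil a unique number, so visits can be linked.

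Section 2.6.1 (Quantitative Analysis) says of the outcomes: "Differences between the two groups from baseline to follow-up will be analyzed using a one-way ANOVA and ANCOVA adjusted for covariates". The t-test, Mann–Whitney and chi-square tests are reserved "to compare the general characteristics between the groups". T0, T1 and T2 appear there only for the reporting of means and standard deviations. The article names no paired test, repeated-measures ANOVA, mixed model or group-by-visit term.

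**The concern.** The aim in section 2.5 is a statement about change in an effect between two visits. It needs a test or an estimate of the group effect at T2 minus the group effect at T1. The method in section 2.6.1 has one factor, which its own sentence identifies as group, and it measures from baseline. It therefore gives one answer for T0 to T1 and another for T0 to T2, with nothing that compares them.

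Two faulty inferences become likely. If one visit is significant and the other is not, a constant effect may be reported as one that appears late or fades. If a T1–T2 difference is looked at and is not significant, the rule in section 2.5 invites the reading that a ceiling was reached, although absence of significance does not show absence of change. The timing aim is at stake. The group comparison at a single follow-up is not.

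**Working it through.** **Scale from the plan's own figure.** Section 2.3 gives 48 per group from a difference of 98.1 min of weekly MVPA, alpha 0.05 and power of at least 0.8, without an SD. Solving backwards (two-sided, normal approximation): d = (1.960 + 0.842) × √(2/48) = 0.572, so SD = 98.1/0.572 ≈ 171.5 min. The 48 can be neither confirmed nor refuted without the SD. It is used here only to set an effect size of 0.57 SD.

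**Other inputs.** 76 per group is half of the 153 enrolled (section 2.2). The split by arm is not in the text, so equality is assumed, with no loss to follow-up. The within-child correlation r is not given; 0.4, 0.6 and 0.8 are assumed, equal for all pairs of visits. An effect of 0.3 SD is added as a smaller case. Class clustering is left out, to isolate this point.

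**Formulas.** Let d be the true effect, the same at T1 and T2, in SD units. The expected z at each visit is d × √(n/2) / √f.
- Change score: f = 2(1 − r). The T1 and T2 tests share the baseline; their covariance is 1 − r and their variance 2(1 − r), so they correlate 0.5.
- Baseline-adjusted ANCOVA: f = 1 − r². The correlation of the two tests is r(1 − r)/(1 − r²) = r/(1 + r).

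P(exactly one visit significant) = 2 × [P(one given visit significant) − P(both significant)], from the bivariate normal distribution.

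**One case in full.** Change score, n = 48, r = 0.4: z = 0.572 × √24 / √1.2 = 2.802/1.095 = 2.56. Power per visit is about 72.5% and both are significant in about 58.8%, so exactly one in 2 × (72.5 − 58.8) ≈ 27%.

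**Exactly one visit significant, constant true effect (%), r = 0.4 / 0.6 / 0.8**

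| Effect | n per group | Change score | ANCOVA |
|---|---|---|---|
| 0.57 SD | 48 | 27 / 16 / 1 | 20 / 10 / 1 |
| 0.57 SD | 76 | 14 / 4 / <1 | 5 / 1 / <1 |
| 0.3 SD | 48 | 27 / 32 / 31 | 38 / 38 / 31 |
| 0.3 SD | 76 | 32 / 33 / 20 | 41 / 35 / 18 |

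Simulated t-tests and ANCOVAs agree to within about two points. Their ranges are 1–29% (0.57 SD, n = 48), 0–16% (0.57 SD, n = 76) and 18–42% (0.3 SD). In the same simulations a direct group test on each child's T2 minus T1 value rejects in about 5%, whatever the effect size or r.

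**Non-significance as a ceiling.** The T2-minus-T1 difference in group effect has standard error √(4(1 − r)/n) SD. At n = 76 this is 0.178 / 0.145 / 0.103, so the 95% CI half-width is 0.35 / 0.28 / 0.20 SD. At n = 48 it is 0.44 / 0.36 / 0.25 SD. A non-significant result can therefore leave open a further gain as large as the 0.3 SD effect considered above, so the interval has to be shown.

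**The case against.** The strongest defence is that the sentence in section 2.6.1 makes group the factor and works from baseline. A change score or a baseline-adjusted follow-up gives one value per child per test, so no separate within-child term is needed and the error term is sound with respect to repeated visits. That stands.

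A reader might infer more: that the one-way ANOVA will be run with visit as the factor, treating a child's three measurements as three children. The error term would then be wrong and conservative. Simulated power for a 0.3 SD change from T1 to T2 with 76 children would be 44 / 42 / 40%, against 65 / 83 / 99% with a within-child error term (r = 0.4 / 0.6 / 0.8). The article does not say that visit is the factor, so neither the wrong error term nor these losses can be charged to the plan.

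It is also fair to say that the named method could be applied to the T1-to-T2 change, which would test the increment directly. Nothing prevents that, but nothing states it, and the sentence fixes baseline as the starting point.

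At the enrolled size and a 0.57 SD effect, the risk of a discordant pair is modest and, with high r, negligible. That stands too; the size depends on effect and r.

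Finally, a condensed article may leave contrasts to a fuller plan. Here, however, it states both a question with a decision rule and a method, and the two do not meet.

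**Conclusion.** The point holds as a gap between aim and method: section 2.5 commits the study to a conclusion about T1 versus T2, and section 2.6.1 names no analysis that yields it. The documents do not support the stronger statement that the outcome analysis has an invalid error term or that real change will be missed.

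Reading timing from visit-by-visit significance would mislead in anything from almost no trials (0.57 SD, r = 0.8) to about two in five (0.3 SD, r = 0.4, baseline-adjusted). A direct contrast holds the error near 5% throughout. These figures rest on an assumed r of 0.4–0.8, equal arms, no loss to follow-up, an identical true effect at T1 and T2, and no class clustering.

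**What to change.** In section 2.6.1, replace the one-way ANOVA/ANCOVA sentence with a linear mixed model for each outcome measured at T0, T1 and T2: fixed effects for group, visit and group-by-visit, a random effect for child, and class accounted for. Class is needed because section 2.2 shows that participation was decided class by class, and section 2.3 says that the sample size ignored the nesting. A class effect that is constant over visits cancels from the T2-minus-T1 contrast, so class-by-visit variation should be allowed for as well.

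Report the group effect at T1, the group effect at T2, and their difference with a 95% CI. In section 2.5, base the cumulative-versus-ceiling statement on that difference and its interval, not on a non-significant T1–T2 comparison.

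The cost is a few sentences and slightly more analysis work. The data, the pupil identifiers and SPSS are already in place, and no new measurement is needed.

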## 2. Materials and Methods

### 2.1. Study Design

The I-MOVE study is a school-based intervention study with a quasi-experimental design (controlled studies in which exposure was assigned by the investigator without using randomization) [20]. The current project was based on a feasibility pilot study [21] and a meta-analysis on the evaluation of school-based interventions [17]. Findings from both were used to design, structure, manage and organize the I-MOVE study. This intervention trial follows the guidelines of the SPIRITS (Standard Protocol items for intervention trials) Checklist.

The I-MOVE study was endorsed by the University of Bologna (Italy).

The administration of the study was designed to allow effective collaboration and communication among different departments of the University of Bologna.

The study was approved by the University of Bologna Bioethics Committee, on the 18th March 2019 (Prot. n. 0054382 of 18/03/2019-[UOR: SI017107-Classif. III/13]). The study was conducted following the Declaration of Helsinki and approved by the school board.

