### 2.2. School and Participant Recruitment

The study setting was a primary school in the city of Imola (70,075 inhabitants, Bologna, Northern Italy).

Invitation letters accompanied by an expression of interest form were sent to the principals of 4 schools of the city of Imola. One school expressed interest in participating in the project. After that, a member of our team visited the interested school to give a global view of the project in front of the relevant staff. Furthermore, a specific meeting with the headmaster was held to obtain the school’s agreement. Finally, we organized a presentation day to explain the project to the teachers. Ten teachers of 5 classes out of 15 agreed to be involved in the project. They attended a training course of 8 h to learn the basis of the project and the practical part of the active breaks intervention. The parents of the children received a short brochure describing the study, and an invitation to attend an informative meeting at school. The purpose of the meeting was to explain the intervention that would be carried out in the classrooms. At the end of the meeting informed consent was obtained from parents/tutors.

The I-MOVE study established the following inclusion criteria: (i) studying in 1st to 5th grade (aged 6–11 years), (ii) not having health problems or physical disability, which might limit the performance of ABs and (iii) having obtained informed consent of parents and permission for personal data processing.

Finally, 153 children were enrolled in the study (Figure 1). The mean number of children in the classes was 22. Participants were free to retire from the study at any point without giving explanations.

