### 2.3. Sample Size

Sample size was estimated considering the actigraph accelerometers as a primary outcome measure of the study. Sample size calculations were based on the pilot and feasibility study [21], which detected a mean difference of 98.1 min in weekly total MVPA, measured using the accelerometer, between the intervention group and control group.

Considering an alpha error of 0.05 and a power of at least 0.8, the minimum size of the sample was estimated as 48 participants per group, for a total of 96 participants, without considering the nested data structure. Power analysis was carried out with Clinicalc.com.

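### The group effect is tested child by child with one-way ANOVA and ANCOVA although whole classes receive the intervention, so the 5% error rate is exceeded whenever outcomes correlate within class

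*Protocol article*

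**What the plan says.** Section 2.6.1 names the tests. For the intervention effect: "Differences between the two groups from baseline to follow-up will be analyzed using a one-way ANOVA and ANCOVA adjusted for covariates". A result counts as significant only if the p "value will be lower than 0.05". The covariates are not listed. The t-test, Mann–Whitney and Chi-square tests are reserved for comparing the groups' general characteristics.

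Section 2.2 describes how the intervention groups arose: "Ten teachers of 5 classes out of 15 agreed to be involved in the project". It also gives a mean class size of 22 and 153 children enrolled. In sections 2.4 and 2.7 the teacher leads the breaks for the class, chooses exercises together with the pupils, and may adapt or add to them.

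Section 2.3 sets the sample size for a 5% type I error and 80% power or more: "the minimum size of the sample was estimated as 48 participants per group, for a total of 96 participants". The same sentence concedes that the calculation was made "without considering the nested data structure".

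**The concern.** Children in one class share a teacher, a grade, a timetable and that teacher's version of the breaks. Their outcomes are likely to be correlated, and the classes span grades 1 to 5, over which fitness, motor and memory scores would be expected to change. One-way ANOVA and ordinary ANCOVA treat each child as an independent observation. Differences between a handful of classes are then measured against child-to-child variation only, so a group difference can reach p < 0.05 with no intervention effect.

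The article recognises the nesting in section 2.3 but takes it up neither there nor in section 2.6.1. This is a named analysis that does not fit the described design, not a detail left out.

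**Working it through.** **The plan's own figure.** For two means, n per group = 2 × (1.96 + 0.84)² × SD² / difference². The difference is 98.1 min of weekly MVPA (section 2.3). No SD is given, so the 48 per group cannot be reproduced directly. Solving backwards, 48 results from a two-sided test if the SD is about 169.8 to 171.5 min, a standardised difference of about 98.1/171.5 = 0.57.

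**Inputs for the error rate.**
- Nominal two-sided level 0.05. Section 2.6.1 gives 0.05; two-sided is an assumption.
- Class size 22 (section 2.2).
- Children analysed per class, m: not given. Consent was individual and accelerometer data need minimum wear time (section 2.5.1), so m may be below 22. I use 22, 15 and 9.
- ICC: not given. I use 0.01 to 0.10.

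**Formulas.** Design effect DEFF = 1 + (m − 1) × ICC. Actual type I error of the child-level test = 2 × [1 − Φ(1.96/√DEFF)].

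Example with m = 22 and ICC 0.05: DEFF = 1 + 21 × 0.05 = 2.05; 1.96/√2.05 = 1.37; type I error 17.1%.

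| ICC (assumed) | m = 22: DEFF, error | m = 15: DEFF, error | m = 9: DEFF, error |
|---|---|---|---|
| 0.01 | 1.21, 7.5% | 1.14, 6.6% | 1.08, 5.9% |
| 0.02 | 1.42, 10.0% | 1.28, 8.3% | 1.16, 6.9% |
| 0.05 | 2.05, 17.1% | 1.70, 13.3% | 1.40, 9.8% |
| 0.10 | 3.10, 26.6% | 2.40, 20.6% | 1.80, 14.4% |

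**Check by simulation.** I simulated unadjusted child-level tests under no effect, with a random class effect and 20,000 runs per setting. With two groups the t-test and one-way ANOVA are the same test. For ICC 0.01, 0.02, 0.05 and 0.10:
- 5 v 2 classes of about 22 (153/22 = 6.95, so about 7 if whole classes enrolled): 7.3%, 10.1%, 17.2%, 26.9%.
- 4 v 3 classes of about 22: 7.3%, 10.4%, 17.0%, 26.7%.
- 5 v 5 classes of about 15: 6.4%, 8.5%, 13.8%, 21.7%.
- 5 classes of 22 v 5 of about 9: 6.0%, 7.6%, 11.6%, 18.0%.

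**Power of a valid class-level test.** Assume 5 v 2 classes of 22 and a standardised difference of 0.57. In SD units, the variance of a class mean is ICC + (1 − ICC)/22. The standard error of the difference is √[that variance × (1/5 + 1/2)]. The test has 7 − 2 = 5 degrees of freedom (critical t 2.57).
- ICC 0.02: variance 0.0645, SE 0.213, power about 58%.
- ICC 0.05: variance 0.0932, SE 0.255, power about 44%.
- ICC 0.10: variance 0.1409, SE 0.314, power about 31%.

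These figures are before any gain from baseline adjustment.

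**The case against.** The strongest defence is that a fuller protocol or analysis plan may contain a class term. That would settle the matter if so, but the article names its tests and thresholds, and as written they are child-level. Nor do the unspecified covariates repair this: class entered as a fixed covariate is fully confounded with group.

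The objection to the size carries more weight. A reader might infer that the false-positive rate simply is 10% to 27%. The documents do not support that. It needs an ICC of 0.02 to 0.10 and about 22 analysed children per class, and neither is stated; the number of control classes is also not in the text. The calculations cover the unadjusted test only. ANCOVA may leave a smaller residual ICC and so a smaller inflation.

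Other stronger readings also fail:
- The t-test is not planned as a test of the effect.
- The section does not mention confidence intervals, although intervals from the same model would be too narrow for the same reason.
- One might infer that the one-way ANOVA compares raw follow-up values and so carries over starting differences. The wording about differences from baseline to follow-up can equally mean change scores.
- Section 2.1 describes the design type as "controlled studies in which exposure was assigned by the investigator without using randomization", whereas section 2.5.10 will ask control teachers "the reason why they chose not to perform active breaks". That tension concerns self-selection and confounding. It is a separate issue that modelling class does not cure, and it adds no weight here.

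**Conclusion.** The point stands. The analysis named in section 2.6.1 ignores class, and its actual type I error exceeds 5% for any outcome with a positive within-class correlation. Over the table's assumptions the rate for an unadjusted test runs from about 6% (ICC 0.01, 9 analysed per class) to about 27% (ICC 0.10, 22 per class). Confidence is high that class is omitted from the stated tests and that this matters. The exact size is uncertain, because it rests on assumed ICCs and assumed numbers analysed per class. The change should be made before the effect analyses are run, since a p-value just under 0.05 from the stated tests could not be taken at face value.

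**What to change.** In section 2.6.1, replace the one-way ANOVA and ANCOVA for the effect analyses with a linear mixed model for each continuous outcome (MIXED in the named SPSS):
- Response: T1 and T2 values.
- Fixed effects: group, time, group × time, the child's T0 value where measured, age and sex.
- Random intercepts for class and child.
- Satterthwaite or Kenward–Roger degrees of freedom, because classes are few.

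Add a check on baseline-adjusted class means with (number of classes − 2) degrees of freedom. Omit the T0 term for time-on-task, which Table 2 shows only at T1 and T2. Use a matching generalised mixed model for categorical outcomes such as weight status. Keep the t-test, Mann–Whitney and Chi-square tests for general characteristics, as planned.

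The cost is more than rewording. P-values will be larger, and power will be lower than the stated 0.8 implies; the class-mean calculation above shows how far it could fall under a 5 v 2 layout. The article should say so. The revised model gives a more honest error rate but does not remove confounding from teachers' choice to take part.
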